## Methods

This study was funded as an R61 pilot award and aimed to establish proof of the concept that SS, measured as area-level differences among groups, is associated with neurocognitive mechanisms of substance use risk. R61 studies are awarded to conduct exploratory research that will provide evidence for a second phase of research. The goal of this R61 is to provide initial results to support funding for a larger study with the goal of replicating the association between SS and neurocognitive mechanisms of substance use risk, additionally testing the relationship between area-level SS and substance use risk, substance use, and examining the role of protective factors at the structural and family level.

### Participants

We will invite 72 children from the second generation of the BYS, aged 11–14 years old, 50% female, 50% from the South Bronx cohort, 50% from the San Juan cohort, and at least 1 parent, to participate in the proposed pilot study by providing residential history (parental report) and belief in a just world (child report) via interview, delay discounting task performance and neural correlates via an MRI scan.

**R61 Specific Aims, Proof of Concept of a relationship between SS and Neurocognitive Mechanisms of Substance Use:**

**Aim 1, Hypothesis 1, SS & brain structure:** Higher levels of SS, as measured by our substance use-relevant SS composite, will relate to adolescent brain structure, Figure 1 including lower volume of superior frontal gyrus, dorsal lateral and medial prefrontal cortices.

**Figure 1 F1:**
[figure not shown]
R61 phase aims. Hypotheses: A substance-use specific composite of structural stressors will relate to brain structure, steeper delay discounting (DD), DD–related brain function, and belief in a just world. DD is theorized to develop alongside belief in a just world, as it is sensible to wait for larger rewards in a just world, where people get what they deserve. Steeper DD may be an adaptive response to an environment high in structural stressors. However, steeper DD is also an established correlate of SUD, and thus, this adaptive response to the environment could increase substance use risk.

**Aim 2, Hypothesis 2, SS & DD:** We expect that greater SS will relate to steeper DD, and less DD-related brain activity in dorsal medial prefrontal cortex, anterior cingulate cortex, insula and ventral striatum. We will use the SS composite variable as a predictor and task-related brain activity in regions of interest (ROIs) as the outcome.

**Aim 3, Hypothesis 3, SS & BJW:** Greater SS composite will relate to weaker BJW.

A moderate effect size association (r > 0.30) found for Hypothesis 1, Hypothesis 2, or Hypothesis 3 will justify progression to the R33 phase.

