However, steeper DD has also been associated with later alcohol use (64) and with SUD diagnosis (65–67). This is theorized to occur when a future outcome (e.g., being able to focus in class the next day, or avoiding a hangover) is devalued and a more immediate reward, (e.g., enjoying alcohol) is chosen (68). Thus, in the context of SUD research, steeper DD has been interpreted as a sign of maladaptive impulsivity, while waiting for larger, later rewards is assumed to be optimal behavior. While steeper DD may be an adaptive strategy in contexts where long-term investments do not pay off, such as areas characterized by high levels of SS, when the reward in question is a substance, and immediate use is chosen over long-term health, this adaptation to the environment could increase the odds of negative outcomes related to substance use (69).

Neuroscience research describing the neurodevelopment of children and adolescents has had a significant impact on policy. More specifically, studies demonstrating the effect of poverty on neural structure in childhood were cited in policy briefs and reports supporting child tax credits (70–73). Furthermore, research demonstrating the differences between adolescent and adult brains helped to form Supreme Court decisions protecting individuals who committed crimes during adolescence from punishments such as the death penalty and life sentence without the possibility of parole (74–77). Thus, characterizing the neurocognitive effects of SS on the adolescent brain may provide important support for advocacy for structural interventions, the most direct solution to structural disparities.

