Given the relevance of DD in reward-related decision making and in SUDs, the neural correlates of DD have been examined via meta-analysis. Activity in the dorsal medial prefrontal cortex (dmPFC) and anterior cingulate cortex (ACC) have been associated with reward valuation, while decreased activity in inferior frontal gyrus (IFG/insula) is associated with a stronger preference for immediate compared to delayed rewards (88). Furthermore, activity in the prefrontal and insular regions are key nodes of a brain marker of individual differences in DD task performance, demonstrating their importance for cognitive processes related to this task (89). The ventral striatum (VS) is a reward-sensitive brain region, activity in the VS increases both when a reward is anticipated and when it is received, and previous studies have linked DD-related VS activity with reward value in adolescents (90). Individual differences in DD correlate positively with magnitude of VS activation such that steeper DD was associated with increased activity in VS (91). Individual differences in delay discounting relate to patterns of connectivity seeded in the dorsal prefrontal cortex (92). Ventral striatal connectivity mediates the relationship between DD performance and subsequent negative health outcomes, including increased BMI in adolescents (93), results underlining the centrality of the dorsal PFC and ventral striatum to DD performance. These results from the existing literature suggest that lower task-related activity across regions including dmPFC, ACC, IFG/insula, and VS may be a risk factor for substance use. Experiences of discrimination and social exclusion have been associated with distinct alterations in PFC functioning, and the ACC is likely a key region for processing social exclusion (94, 95). Thus, the dmPFC, ACC, IFG/insula and VS emerge as key brain regions of interest given their association with both substance use and social exclusion.

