Three distinct dual systems models describe diverging growth curves for the neurobiological systems underlying reward sensitivity and cognitive control across adolescence in into adulthood. The Dual Systems Model (96), the Maturational Imbalance Model (97), and the Driven Dual Systems Model (98) all propose that during early adolescence, the reward-sensitive VS develops relatively quickly compared to the slower development of prefrontal regions associated with cognitive control, and this mismatch in development is theorized to explain why adolescence is life stage characterized by increased in risky behaviors, including substance use (98–105). The three dual systems models differ in their hypotheses regarding the growth curves of reward sensitivity and cognitive control during later adolescence and early adulthood, suggesting different outcomes during these later life stages (96–98). However, all three models agree that studying neural activity in reward-sensitive brain regions and prefrontal regions associated with cognitive control can contribute to our understanding of adolescent reward-related decision-making (100). For all these reasons, the dmPFC, ACC, IFG/insula and VS regions are particularly important to study, at this developmental stage, in relation to substance use risk (98, 100, 102–105).

*The Boricua Youth Study: An opportunity to isolate the role of SS on substance use, by controlling for familial factors*.

The Boricua Youth Study (BYS) is an epidemiological study formed with the goal of better understanding the lived experiences of Puerto Rican individuals and their families living in two contexts: the island of Puerto Rico, and the New York City region of the continental US (106). BYS started in 2001 through a collaborative effort between NYSPI/Columbia University, led by [name], and the University of Puerto Rico, led by [name]. BYS originally recruited about 2,500 children and their families based on multistage probability household samples, representative of the two original target populations: Puerto Rican families in the South Bronx, NY and in the metropolitan area of San Juan, Puerto Rico. The original cohort of BYS children were aged 5–13 at the first wave of recruitment and data were collected over 3 Waves, between 2001–2004 (106). A fourth assessment wave, collected during young adulthood, was collected between 2013–2018 (107, 108).

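### The protocol reads lower ventral striatum activity as a substance-use risk marker, but its only directional evidence linking discounting to ventral striatum activity points the other way

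*Protocol article*

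**What the plan says.** Under R61 Specific Aims, Hypothesis 2 has a behavioural half, "We expect that greater SS will relate to steeper DD", and a neural half, "less DD-related brain activity in dorsal medial prefrontal cortex, anterior cingulate cortex, insula and ventral striatum". SS is the predictor and task-related activity in each region of interest is the outcome. The Abstract (Methods) likewise names steeper DD and reduced activity in reward-sensitive regions together as mechanisms of substance use risk.

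The Background gives the reasoning:

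- On VS and discounting: "Individual differences in DD correlate positively with magnitude of VS activation such that steeper DD was associated with increased activity in VS".
- On the inferior frontal gyrus and insula: "decreased activity in inferior frontal gyrus (IFG/insula) is associated with a stronger preference for immediate compared to delayed rewards".
- Later in the same paragraph, the cited results are said to "suggest that lower task-related activity across regions including dmPFC, ACC, IFG/insula, and VS may be a risk factor for substance use".
- On which end of DD carries risk: "steeper DD has also been associated with later alcohol use", and also with SUD diagnosis.

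The Aims section closes with the progression criterion: an association of r > 0.30 for Hypothesis 1, 2 or 3 justifies the R33 phase.

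**The concern.** The inference that lower activity marks risk follows for the IFG/insula, where less activity goes with preferring the immediate reward. For VS it reverses the finding reported a few sentences before. Since the protocol treats steeper DD as the risk end of the scale, its own VS evidence places lower VS activity with shallower discounting, the lower-risk end.

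The stake is interpretation. The study exists to show that SS relates to mechanisms of substance use risk, and its result feeds a funding decision. If a negative SS-VS association appears, the text as it stands invites the authors to call it such a mechanism, although nothing cited connects lower VS activity with steeper discounting or with substance use.

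**Working it through.** The documents state signs here, not sizes, so there is no planned figure to reproduce. The check sets the signs side by side and then asks what they imply jointly.

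**Step 1: the signs**

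| Link | Sign | Where stated |
|---|---|---|
| SS with DD steepness | + | Hypothesis 2 |
| SS with VS activity | − | Hypothesis 2 |
| DD steepness with VS activity | + | Background, neural correlates of DD |
| DD steepness with substance use | + | Background, DD and later alcohol use and SUD |
| VS activity with substance use risk | − | Background, inference only; Abstract |
| Deprivation or low SES with reward response | − | Background, studies of SES and area deprivation |

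The third and fourth rows together suggest a positive VS-risk link through DD. The fifth row asserts a negative one. The remaining VS statements in that Background paragraph (activity tracking reward value, connectivity as a mediator) carry no sign that would support the fifth row. Nor does the dual-systems paragraph, which explains adolescent risk by a mismatch in which "the reward-sensitive VS develops relatively quickly compared to the slower development of prefrontal regions associated with cognitive control".

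**Step 2: what the signs imply together**

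Let a = r(SS, DD), b = r(DD, VS) and c = r(SS, VS). Assumed ranges are a = 0.30 to 0.35 (near the progression criterion and the stated detectable r), b = +0.30 to +0.50 (sign from the Background, size assumed) and c = −0.30 to −0.35 (a result of the predicted sign at about the criterion).

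- SS-VS correlation implied through DD alone: a × b. Low end 0.30 × 0.30 = +0.09; high end 0.35 × 0.50 = +0.175.
- Direct SS effect on VS given DD: (c − ab)/(1 − a²). Low end (−0.30 − 0.09)/0.91 = −0.43; high end (−0.35 − 0.175)/0.8775 = −0.60.
- Indirect effect through DD: a × (b − ac)/(1 − a²). Low end 0.30 × 0.39/0.91 = +0.13; high end 0.35 × 0.6225/0.8775 = +0.25.

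**Step 3: can both halves of Hypothesis 2 hold?**

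Yes. For given a and b, c can lie anywhere in ab ± √[(1 − a²)(1 − b²)]. With a = b = 0.30 this is 0.09 ± 0.91, or −0.82 to +1.00. Over all the combinations above, the smallest eigenvalue of the correlation matrix is 0.195 to 0.40, so every one is valid. A negative SS-VS result would then reflect a route from SS to VS that does not pass through DD and works against the part that does.

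**Step 4: how well could the sample settle the DD-VS sign?**

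At n = 72 the standard error of Fisher's z is 1/√69 = 0.120. An observed DD-VS correlation of 0.30 (z = 0.310) has a 95% interval of z = 0.074 to 0.546, or r of about 0.07 to 0.50. That is useful for interpretation but too imprecise for a pass/fail rule.

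**The case against.** The strongest defence is that Hypothesis 2 concerns exposure. It relates SS to regional activity and makes no claim about DD and VS. The evidence bearing on that sign is the deprivation literature, and the Background cites studies finding weaker neural reward responses at lower SES and in deprived neighbourhoods. This stands: the predicted SS-VS direction has support.

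Three stronger readings are tempting, and the document supports none of them.

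- *The two halves of Hypothesis 2 contradict each other.* They do not. Correlations need not be transitive, and Step 3 shows that they can coexist.
- *A positive SS-VS association would count as failure.* No one-sided test is specified, the criterion is written as r > 0.30 with no rule for the sign of each outcome, and the Figure 1 caption gives no direction for brain function.
- *VS alone would trigger R33.* The criterion refers to Hypothesis 2 as a whole and does not say whether one region suffices.

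It is also fair that the cited DD-VS relation may not carry over. In-scanner trials are built around each child's own discount parameter, and the cited study's task cannot be checked from this document. The protocol hedges its inference and describes itself as exploratory.

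These points limit the concern but do not remove it. The Abstract and the Background do present reduced reward-region activity as a risk mechanism, and the deprivation studies, which concern exposure, do not supply that link.

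**Conclusion.** The concern holds as a flaw in rationale and interpretation. The document offers no directional evidence that lower VS activity marks steeper discounting or higher risk, and its one directional DD-VS finding points the opposite way. A negative SS-VS association should therefore not by itself be read as proof of a risk mechanism under the r > 0.30 criterion. How that criterion treats sign, or a single region, is unstated.

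The reach is one of four neural regions in Hypothesis 2. The IFG/insula evidence agrees with the hypothesis, and for dmPFC and ACC the Background gives no opposing DD direction. DD behaviour and Hypotheses 1 and 3 are untouched. The sign argument rests on the Background's own summary of the DD-VS finding; the path values rest on assumed correlation sizes and serve only as illustration.

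**What to change.** 1. Reconcile the Abstract, the Background paragraph on neural correlates of DD, and Hypothesis 2. Either base the VS direction explicitly on the deprivation evidence and remove VS from the inference that lower activity marks risk, or state no direction for VS.
2. Pre-specify that the within-sample correlation between VS activity and log(k), with its interval, will be reported beside any SS-VS association to interpret its sign. The calibration task already yields k for each child.
3. State that a VS association alone does not establish a risk mechanism for R33 progression.
4. Do not make progression conditional on the VS-log(k) correlation; at n = 72 it is too noisy for a hard gate.

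Possible wording:

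> The expected SS-VS direction rests on studies of deprivation and reward response. Because steeper DD has been linked to greater VS activity, an SS-VS association will be interpreted together with the VS-log(k) correlation in this sample and will not on its own be taken as evidence of a substance-use risk mechanism.

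The cost is a few sentences and one further correlation from data already planned. The trade-off is that one of the four neural regions carries less weight on its own. The change is best made before any results are seen.

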### Measurement of SS

To determine the role of SS on substance use risk in adolescents, we will create a composite measure of substance use-relevant SS. This composite will be based on area-level racial group differences in income, education, and exposure to violence, as exposure to lower levels of income and education, and higher levels of violence have been related to increased risk for substance use (2–9). To calculate SS SU-relevant measures of income and education, we will use the Index of the Concentration at the Extremes using income and education, using data from the US census. For example, for income, within each census tract (i) our participants live in, the ICE_income_ will be calculated as the number of White individuals in the top income quintile (Ai) minus the number of racially minoritized individuals in the bottom income quintile (Pi), divided by the total population across all income quintiles (Ti; Figure 2).

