#### Assessment of DD behavior and neural correlates

We will use an fMRI-adapted DD task previously used with adolescents to collect a DD performance and related brain activity. This task has good test-retest reliability for behavior and neural response (123). Like other monetary DD tasks, on any given trial, participants are asked to decide between a smaller sooner reward, or a larger later reward. Participants will first perform a calibration task comprised of 50 trials to assess each individual child's discount parameter *k* outside of the scanner. This discount parameter is used to create 90 trials presented in the scanner, in which the participant can be expected to choose the smaller, sooner reward half of the time, providing adequate data to examine neural response to smaller soon and larger later rewards. Participants are told that they will be paid the amount of one of their choices after the task is completed.

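### The R33 progression rule (r > 0.30 for any of three hypotheses) fixes neither direction nor deciding outcome, and the composite's coding is left unclear

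*Protocol article*

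**What the plan says.** The rule closes the R61 Specific Aims: "A moderate effect size association (r > 0.30) found for Hypothesis 1, Hypothesis 2, or Hypothesis 3 will justify progression to the R33 phase".

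The hypotheses in the same section state directions:
- Hypothesis 1: more SS goes with "lower volume of superior frontal gyrus, dorsal lateral and medial prefrontal cortices".
- Hypothesis 2: "greater SS will relate to steeper DD, and less DD-related brain activity in dorsal medial prefrontal cortex, anterior cingulate cortex, insula and ventral striatum".
- Hypothesis 3: "Greater SS composite will relate to weaker BJW".

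Measurement of SS defines the income component as "the number of White individuals in the top income quintile (Ai) minus the number of racially minoritized individuals in the bottom income quintile (Pi"), over the total population. Education is built in the same way. The violence component is a difference between White and minoritized murder counts, in that order, over the precinct population. The section states no sign reversal.

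The discounting task is calibrated "to assess each individual child's discount parameter *k* outside of the scanner"; a higher k is steeper discounting. Statistical analyses describes covariate-adjusted models but does not say whether the r in the rule comes from them. Power analysis says that this phase is judged on effect size rather than significance.

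**The concern.** A rule based on effect size depends on which r, which sign and which outcome. Here all three are open. The components are high where a tract is advantaged, while the hypotheses need high to mean more stress. The predicted signs are mixed, even within Hypothesis 2. Nothing says how many of several outcomes must meet the threshold for a hypothesis to count.

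At stake is the decision to start the R33 phase. Taken literally as a signed r, the rule cannot credit some results that support the hypotheses, and it credits their opposites. Taken as |r|, it credits both. If these choices are made after the data are seen, they become a choice among nine outcomes and two signs.

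**Working it through.** **1. The plan's own figure.** Power analysis gives n = 72, 80% power and r = 0.35. Alpha is not stated; I assume two-sided 0.05. Power = Φ(atanh(0.35)·√(72−3) − 1.96) = Φ(0.3654 × 8.307 − 1.96) = Φ(1.076) = 85.9%. The smallest r detectable at 80% is 0.325. With 10 covariates partialled out, √59 replaces √69 and power is 80.2%. The stated figure is therefore conservative for a plain correlation and about right for an adjusted one. It is not part of the problem.

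**2. Predicted signs.**

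| Outcome | Number | Composite high = more SS | Components as written (high = advantage) |
|---|---|---|---|
| Prefrontal volumes (H1) | 3 | − | + |
| Discounting by k (H2) | 1 | + | − |
| Regional activity (H2) | 4 | − | + |
| Belief in a just world (H3) | 1 | − | + |

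The total is 3 + 5 + 1 = 9. A signed r > 0.30 fits one of nine in the first coding and eight of nine in the second. In the first coding, a result that supports the hypotheses can pass only through discounting. If its true r were 0.35, the chance of an observed r above 0.30 at n = 72 (unadjusted) is 68%, however strongly H1 and H3 were supported.

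**3. Chance of a go with no association.** For one correlation, t = 0.30·√(df/0.91) with df = n − 2 − covariates. The named covariates are four familial factors, unfair treatment, age, sex, diagnosis and adverse childhood experiences (9), plus ADHD medication for neural data (10).
- n = 72, none: df = 70, t = 2.63, P(|r| > 0.30) = 1.05%, one direction 0.52%.
- n = 72, 10 covariates: df = 60, t = 2.44, 1.78% and 0.89%.

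For any of nine, I simulated correlation 0.5 within the three volumes and within the four regional activities, and independence otherwise (an assumption). Three directional outcomes use 1 − (1 − p)³ with p one-sided, taking them as independent.

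| Setting | Any of 9, \|r\| | Any of 9, hypothesised direction | One directional outcome per aim (3) |
|---|---|---|---|
| n = 72, no covariates | 8% | 4% | 1.6% |
| n = 72, 9–10 covariates | 13–14% | 7% | 2.5–2.7% |
| n = 58, 10 covariates (assumed loss of about 20%) | 27% | 14% | 5.6% |

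If all nine were independent, the first column would be 9.0%, 14–15% and 29.6%.

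**4. Precision.** An observed r of 0.30 at n = 72 has a 95% confidence interval of 0.07 to 0.50 (unadjusted).

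**The case against.** The best defence is that the rule speaks of a moderate effect size, which is the language of magnitude, and of an association found for a hypothesis, which ties it to the stated directions. The aims also speak of higher SS as measured by the composite, so the intended orientation is plain, and how components are scaled and combined may sit in the fuller protocol. Much of this stands. A reader might infer that the rule has the wrong sign. That follows only from the literal signed reading; the supportable charge is that direction is not fixed. Intent does not settle it, because the article defines the components in the opposite sense and the rule itself carries no direction.

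A reader might also infer that the rule cannot tell signal from chance. At n = 72 that is not so: |r| > 0.30 on one outcome corresponds to p of about 0.01, stricter than 0.05 (critical r = 0.232). The 27% figure rests on an assumed loss of scans for which the article gives no number.

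The Background reports that "steeper DD was associated with increased activity in VS", while Hypothesis 2 expects steeper discounting and less ventral striatum activity with greater SS. It is tempting to call this a sign error. Hypothesis 2 links SS to each outcome separately, and the Background also cites blunted reward responses in deprived areas. It is a tension in the evidence, and it shows why direction needs stating.

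Finally, the phase is deliberately exploratory and based on effect size. That answers a demand for significance or multiplicity control. It does not answer the absence of a sign or a deciding outcome.

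**Conclusion.** The concern holds as a badly fixed rule. With discounting scored by k, no coding of the composite makes one signed r > 0.30 fit all nine outcomes. Read as |r|, a wrong-direction result on any one of nine is enough for a go; the text does not require this reading but does not exclude it. Comparing nine outcomes with nine, stating direction alone roughly halves the false-go rate, from about 8% to 4% unadjusted and from 13–14% to 7% with the plan's covariates. Naming one outcome per aim lowers it further, to about 1.5–3%. These figures assume 72 evaluable children and the correlations given above; with fewer usable scans all of them rise.

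**What to change.** In the R61 Specific Aims and Measurement of SS:
- State that the composite is reverse-scored so that higher means more SS.
- Write the expected sign beside each of the nine outcomes.
- Require r of at least 0.30 in magnitude in the hypothesised direction.
- Name one deciding outcome or summary per aim: for example mean prefrontal volume for Aim 1, discounting or mean regional activity for Aim 2, and the belief in a just world score for Aim 3.
- Say that r is the covariate-adjusted partial r, and report its confidence interval.

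No Holm-adjusted significance condition is needed, given the stated focus on effect size, and regional activity can remain the deciding outcome for Aim 2.

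The cost is wording and a slightly harder go. If the true r is 0.35 for all three deciding outcomes, each passes with probability 68% (n = 72, unadjusted), so at least one passes with probability 1 − 0.32³ = 97% if they are independent. If only one aim has such an effect, the chance is about 68%. The change should be made before outcome data are seen.
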